#### During study monitoring and support

1. Study Monitoring and Data Fidelity Checks: The sponsor or its representative may visit the study facilities at any time (remotely and /or in person) in order to maintain current and personal knowledge of the study through review of the records, comparison with source documents, observation and discussion of the conduct and progress of the study. The clinical site will permit trial-related monitoring, audits, IRB/IEC review, and regulatory inspection(s) by providing direct access to source data/documents.
2. Fidelity Checks: As part of study monitoring, we will conduct ongoing fidelity checks for the primary outcomes (and other variables of interest). During fidelity checks, records will be pulled randomly. If errors in coding the variables are observed, the nature of the error will be evaluated to determine whether study procedures need to be updated to improve clarity (though unlikely as we are using methodologies established in prior work) and/or staff require additional training in how to capture the study variables.

Procedures for participants who drop out or are lost to follow-up

If subjects drop out or are lost to follow-up, there will be agreements with the subject per the Informed Consent that the research staff can access different sources of information other than medical records. Additional sources of information will be the persons listed as individuals the research staff may reach out to if the research staff cannot contact the participants. We will also obtain permission to request medical records from other treatment facilities if the primary outcome or adverse event is reported at another treatment facility. See prior discussion regarding ensuring final study assessments be performed if possible before withdrawal of consent.

### 11.5 STOPPING RULES

A Data Safety and Monitoring Board (DSMB) will have oversight over the three stopping rules proposed below. Though we have proposed stopping rules within this protocol, the DSMB will finalize the stopping rules for safety. Safety Monitoring will be guided by previous research and study data to determine whether there is an excess of suicide attempts or death. Prior research has shown that, following a suicide attempt, up to half of the patients in treatment make another suicide attempt. If a suicide attempt occurs within the first year of treatment, on average a patient will attempt suicide 2.5 times. Monitoring of suicide attempts will occur by tracking hospitalization records, reviewing medical records, and carrying out interviews at all time points. Other specific strategies for tracking include (1) utilization of research staff ("study managers") to obtain detailed contact information regarding participants' family, friends, clergy, probation officers, and mental health workers and (2) research staff will use medical records and coordinate with the participants' healthcare providers, whenever possible, to track participants over time and to assist with scheduling follow-up assessments. If participants cannot be contacted, family, friends, clergy, probation officers, and mental health workers will be contacted by research staff with permission from the participants. The DSMB may recommend stopping the study if there is:

1. Early demonstration of effectiveness (assessed through the group sequential design) for suicide attempts. Effectiveness boundaries have been fully specified in Appendix C.
2. Early demonstration of lack of effectiveness for Aviva (assessed by specifying the group sequential design with binding futility). Futility boundaries have been fully specified in Appendix C.
3. Determination of unexpected, significant or unacceptable risk to participants by the monitoring committee. Based on historical prevalence of suicide attempts in this target population, we anticipate that up to half of enrolled patients could attempt suicide during a 104 week follow-up assessment period. DSMB will review all suicide attempts for causality to the investigational device, and if there are more SAs in the treatment arm than control arm, the study enrollment will be paused until DSMB can review under this stopping rule.

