|--------------------------------------|-----------------------------------------------------------------------------------------------------------------------------------------------------------------------------------------------------------------------------------------------------------------------------------------------------------------------------------------------------------------------------------------------------------------------------------------------------------------------------------------------------------------------------------------------------------------------------------------------------------------------------------------------------------------------------------------------------------------------------------------------------------------------------------------------------------------------------------------------------------------------|
|                                      | suicide attempts) have occurred. The O'Brien-Fleming spending function is used to determine the effectiveness test boundary. A binding futility boundary is incorporated in this design, also with an O'Brien-Fleming boundary.                                                                                                                                                                                                                                                                                                                                                                                                                                                                                                                                                                                                                                       |

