## 11. STATISTICAL CONSIDERATIONS

### 11.1 STATISTICAL PROCEDURES AND DATA ANALYSIS

#### 11.1.1 Primary Effectiveness: Definition of Success (or Failure) of the Endpoint

The time to first suicide attempt after randomization is the primary endpoint. The study will be a success if the primary endpoint is statistically significant in favor of Aviva (compared to sham app) based on time to suicide attempt, a time-to-event variable. At 90% power, fifty suicide attempts (i.e., event) are expected while following 391 participants for 104 weeks. In anticipation that treatment effects may be observed before 50 suicide attempts occur, the primary endpoint will be tested via a group sequential test with K = 4 Looks using an O'Brien-Fleming like alpha spending function boundary. A non-binding futility boundary is incorporated in this design, also with an O'Brien-Fleming boundary. The Type I error level alpha will be protected at level 0.025 one-sided (which is equal to 0.05 two-sided).

Study failure will be defined as lack of a statistically significant finding for suicide attempts in favor of Aviva. Details are provided below.

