**ATTACHMENT A**

---

*TITLE: Formal Statistical Hypotheses and Mathematical Forms*

- Null Hypothesis:  $HR = 1$ .
- Alternative Hypothesis:  $HR < 1$ .
- Where  $HR$  = Hazard Ratio

By way of background, here is the supportive information from the protocol (see Attachment 0601 IDE Clinical Protocol, page 218):

- Design a group sequential test with four Looks when 60%, 75%, 90% and 100% of the statistical information has been obtained.
- Assume exponential distributions for Group 1 Sham and Group 2 Aviva time to first SA after randomization.  
Set overall Type I error rate to 0.025 for the one-sided alternative hypothesis.  
Set the power to 90% when  $HR = 0.3826$  as reported in Rudd (2015).
- Set the total study time to 24 months.  
Set the accrual time to 12 months.  
Assume uniform accrual of patients over 12 months.  
Assume equal randomization to the Sham and Aviva groups.  
Determine the stopping boundaries for the GST for efficacy and for non-binding futility.  
Determine the number of events needed over time for statistical significance at the end of the study and estimate the sample size in each group when testing the null hypothesis with the log-rank test. N has increased from 374 to 391 because of using the non binding futility instead of binding futility

**ATTACHMENT B***TITLE: Overview of Aviva Product Development*

Given the lack of available FDA cleared and approved products for adults who do not have Schizophrenia and Schizoaffective Disorder, the scientists who developed BCBT/CT-SP (the only proven protocols for reducing suicide attempts in adults at risk) created Aviva. Thus, Aviva has the same theoretical basis as the face-to-face, suicide-specific CBT protocols. As such, sessions and practice exercises are guided by the new understanding that suicidal ideation and attempts emerge from deficits in cognitive, behavioral, emotional, and physical domains. Aviva is designed to reduce attempts regardless of psychiatric diagnosis. The ability to address suicide risk in the absence of other psychiatric diagnoses is significant, as it is estimated that approximately 10-40% of those at risk do not have another mental health diagnosis such as Major Depressive Disorder or Schizophrenia (Asnis et al., 1993). Below is a description of the cognitive, behavioral, emotional, and physical risk factors.

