**PROPRIETARY AND CONFIDENTIAL**

Oui Therapeutics, LLC | [name]

level to detect a hazard ratio of 0.3826 when the group 1 exponential hazard rate is 0.0115 (this gives a group 2 exponential hazard rate of 0.0044). Under these assumptions, the number of events will be 37 and 15 in group 1 and group 2 respectively. The maximum follow-up time for a subject is 24 time units (months) with an accrual period of 12 time units.

These results assume that the group sequential design has 3 interim sequential tests (4 total looks including final analysis). The O'Brien-Fleming spending function is used to determine the effectiveness test boundary. The O'Brien-Fleming spending function is used to determine the non-binding futility boundary.

The drift parameter for this design equals 3.4387. The drift parameter equals the square root of the maximum information level by the log hazard ratio. The ratio of this drift parameter to the drift parameter from the equivalent fixed term design represents the ratio of the sample sizes required for this GST design to that of its fixed term equivalent.

GST Boundaries (Z scale):

Upper effectiveness bounds: 2.6686, 2.3865, 2.1685, 2.0748

Futility bounds: 0.8347, 1.3133, 1.7538, 2.0748

**ATTACHMENT D***TITLE: Mathematical Formulations for Suicidal Ideation*

PASS 2020, v20.0.3 9/10/2020 2:59:16 PM 1

Two-Sample T-Tests Assuming Equal Variance

Numeric Results for an Equal-Variance T-Test \_\_\_\_\_

 $\delta = \mu_1 - \mu_2$ Hypotheses:  $H_0: \delta = 0$  vs.  $H_1: \delta \neq 0$ 

| Power   | N1  | N2  | N   | $\delta$ | $\sigma$ | Alpha |
|---------|-----|-----|-----|----------|----------|-------|
| 0.83582 | 70  | 70  | 140 | 3.8      | 7.6      | 0.050 |
| 0.88160 | 80  | 80  | 160 | 3.8      | 7.6      | 0.050 |
| 0.91559 | 90  | 90  | 180 | 3.8      | 7.6      | 0.050 |
| 0.94043 | 100 | 100 | 200 | 3.8      | 7.6      | 0.050 |

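### The futility boundary is called binding in the synopsis and in stopping rule 2 of section 11.5, but the design actually sized and bounded is non-binding

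*Protocol*

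**What the plan says.** Two places in the protocol describe a binding rule:

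- Synopsis, Statistics Primary Analysis Plan: "A binding futility boundary is incorporated in this design, also with an O'Brien-Fleming boundary".
- Section 11.5, stopping rule 2: "Early demonstration of lack of effectiveness for Aviva (assessed by specifying the group sequential design with binding futility". The next sentence refers the reader to Appendix C (the document is headed Attachment C) for the futility boundaries.

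Three places describe a non-binding rule:

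- Section 11.1.1: "A non-binding futility boundary is incorporated in this design, also with an O'Brien-Fleming boundary".
- Attachment A: "Determine the stopping boundaries for the GST for efficacy and for non-binding futility", and then "N has increased from 374 to 391 because of using the non binding futility instead of binding futility".
- Attachment C, in its title, in its settings table and in its text: "The O'Brien-Fleming spending function is used to determine the non-binding futility boundary".

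All of this is current text. The only boundaries printed anywhere are those of Attachment C: efficacy 2.6686, 2.3865, 2.1685, 2.0748 and futility 0.8347, 1.3133, 1.7538, 2.0748 on the Z scale.

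**The concern.** Binding and non-binding futility are different designs. With a binding rule, the efficacy bounds are solved on the premise that every futility crossing ends the trial. The later bounds can then be lower, and the trial smaller, but the type I error holds only if the premise is kept. With a non-binding rule, the efficacy bounds are solved as if there were no futility boundary, so the DSMB may continue after a crossing without inflating the error.

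The label therefore settles two practical questions. The first is whether the DSMB has discretion once the futility bound is crossed. The second is which option the independent statistician selects if boundaries are recomputed from the spending functions at the actual event counts. Recomputation is likely to be needed, because the planned looks in Attachment C include 31.2 and 46.8 events, which cannot be observed. At present the protocol answers both questions both ways, and the DSMB charter, which section 9.9.1 says is still to be finalised, could inherit either label.

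**Working it through.** **Inputs.** One-sided alpha 0.025 (Attachment A: "Set overall Type I error rate to 0.025 for the one-sided alternative hypothesis"); power 90%; information times 0.60, 0.75, 0.90, 1.00; O'Brien-Fleming spending for alpha and beta; HR 0.3826; sham hazard 0.0115 per month; 12 months' uniform accrual and 24 months in total; 195 sham and 196 Aviva (Attachments A and C).

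**Spending functions.** Alpha: A(t) = 2[1 − Φ(z₀.₉₈₇₅/√t)]. Beta: B(t) = 2[1 − Φ(z₀.₉₅/√t)]. At the four looks:

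- cumulative alpha 0.0038, 0.0096, 0.0181, 0.0250
- cumulative beta 0.0337, 0.0575, 0.0829, 0.1000

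Both rows match Attachment C.

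**Step 1: reproduce the plan (non-binding).** The efficacy bounds were solved by recursive numerical integration with no futility boundary. The futility bounds and the drift were then solved for 90% power.

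- Efficacy 2.6686, 2.3865, 2.1685, 2.0748. Futility 0.8347, 1.3133, 1.7538, 2.0748. Drift 3.4386 (stated 3.4387).
- Events = 4 × drift² / (ln HR)² = 4 × 3.4386² / 0.9608² = 51.24, rounded up to 52.
- Event probability per arm = 1 − (e^(−12λ) − e^(−24λ))/(12λ), which gives 0.1863 for sham and 0.0760 for Aviva, mean 0.1312.
- N = 51.24 / 0.1312 = 390.6, rounded up to 391.

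Every figure agrees with Attachment C.

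**Step 2: the binding design.** The inputs are the same, but the efficacy bounds are solved given that futility crossings stop the trial. The last column keeps the present drift instead of re-solving it for 90% power.

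| | Non-binding (Attachment C) | Binding, 90% power | Binding, drift 3.4387 |
|---|---|---|---|
| Efficacy bounds | 2.6686, 2.3865, 2.1685, 2.0748 | 2.6686, 2.3863, 2.1545, 1.970 | 2.6686, 2.3863, 2.1497, 1.918 |
| Futility bounds, looks 1–3 | 0.8347, 1.3133, 1.7538 | 0.7769, 1.2487, 1.6805 | essentially as Attachment C |
| Drift | 3.4387 | 3.3640 | 3.4387 |
| Events | 51.24 (52) | 49.04 (50) | as now |
| N | 391 | 373.8 (374) | 391 |

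The 374 is the former sample size that Attachment A quotes. This confirms which design each number belongs to.

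**Step 3: operating characteristics (one-sided).**

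| Efficacy bounds used | Futility obeyed | Futility ignored |
|---|---|---|
| Attachment C, type I error | 0.0219 | 0.0250 |
| Attachment C, power | 90.0% | 92.3% |
| Binding at N 374, type I error | 0.0250 | 0.0292 |
| Binding at current size, type I error | 0.0250 | 0.0317 |

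**Step 4: how often the question arises.** Under the null, the chance of crossing futility at look 1 is Φ(0.8347) = 0.798. Under the design alternative it is 0.0337, the first beta increment.

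**Related remnant.** Section 11.1.1 expects fifty events, where Attachment C needs 52. Fifty is the binding design's rounded-up count, so this figure too may have been left over from it.

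**The case against.** The strongest reply is that only one design is printed. N, the event count, the drift and all the boundaries are non-binding, and Attachment A explains the change. Section 11.5 itself sends the reader to those boundaries, so a DSMB following it reaches the right numbers. With those numbers the type I error does not exceed 0.025 whichever label is believed. Inflation needs someone to re-solve the design as binding and the DSMB then to overrule a crossing, which mixes the two readings. The first efficacy bound is identical in both designs and the second differs by 0.0002. The 80% crossing figure applies only under the null. Section 11.5 also says the DSMB may recommend stopping, which is already advisory language.

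All of these points are factually correct, and they limit the numerical harm. The advisory wording is weak evidence either way, because it introduces the efficacy and safety rules as well. What the reply does not remove is the contradiction over whether a futility crossing obliges a stop. The correct numbers in Attachment C do not answer that, and the stopping-rules section gives the opposite answer to section 11.1.1. Nor is a mixture of readings far-fetched when the statistician who recomputes bounds and the board that acts on them may each rely on a different section.

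**Conclusion.** The protocol is wrong as written. The synopsis and stopping rule 2 of section 11.5 describe a binding design that the protocol's own attachments have replaced.

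Used unchanged, the Attachment C bounds keep one-sided type I error between 0.0219 and 0.0250. An error of 0.029 to 0.032 arises only if efficacy bounds are recomputed as binding and futility is then overruled. The two designs differ little in efficacy at looks 1 to 3. The material differences are the final efficacy bound (1.97, or 1.92 at the current size, against 2.0748) and the sample size (374 against 391). When each design is solved for 90% power, the futility bounds at looks 1 to 3 differ by about 0.06 to 0.07.

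These figures assume looks exactly at the planned information fractions and the spending functions named in Attachment C, which reproduce its printed values. The main consequence is operational: the DSMB has two incompatible instructions on a decision it would very probably face at the first look if Aviva has no effect.

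**What to change.** Replace binding with non-binding in the synopsis (Statistics Primary Analysis Plan) and in stopping rule 2 of section 11.5. Add one sentence to section 11.5: efficacy bounds, including any recomputed at actual event counts, are always derived ignoring the futility boundary, as in Attachment C. Put the same statement in the DSMB charter. While editing, reconcile the fifty events in section 11.1.1 with the 52 in Attachment C, and cite the boundaries by one name (Attachment C).

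The cost is a few wording changes and one charter line. N, events, boundaries, alpha and power stay as they are. The change should be in place before the first interim look.

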## 12. APPROACH TO ENSURE INTEGRITY OF DATA TO SUPPORT PRIMARY ENDPOINTS

### 12.1 REDUCE LIKELIHOOD OF PLACEBO EFFECT

- During the consent process, participants will be informed that they will be assigned to "one of two digital interventions." Participants will be informed that both interventions include some combination of supportive listening, education about crisis services, software services and referrals to treatment services. Thus, participants in both conditions will have the expectation that they are participating in a potentially efficacious intervention.
- Participants will be randomized to treatment and control conditions. We will maintain blinding of the participant to treatment through the use of a sham app. The app will be robust as it will include the same number of weekly interactions with subjects (frequency

and duration) as the treatment. The sham app content will include digitized versions of patient information that is typically distributed at discharge.

- We will conduct a blinding assessment. At 104 weeks, we will ask the participant: The blinding index (BI) will be calculated by asking participants: “Do you think you received a suicide prevention app? Why?: (1) Yes (2) No (3) I don’t know”.

#### 12.2 *REDUCE LIKELIHOOD OF SELECTION BIAS IN RECRUITMENT AND ENROLLMENT*

- Recruitment: There will be training sessions that explain the inclusion/exclusion criteria and importance of the study and randomization to the staff.
- Enrollment in treatment arms: As previously noted, we will reduce selection bias by using a randomization procedure that adjusts for factors that may affect outcomes. Our randomization will occur with allocation concealment.

#### 12.3 *REDUCE LIKELIHOOD OF INACCURATE OR BIASED PATIENT REPORTS DURING ASSESSMENTS*

- Participants will be instructed to schedule their phone call during a time when they are free from distractions and can provide reliable and accurate responses.
- Data will be collected by research assessors. The Clinicians (PIs) may be responsible for patient care during study participation, so having independent research assessors helps mitigate the risk of potential bias

#### 12.4 *REDUCE LIKELIHOOD OF STAFF DEVIATING FROM THE DATA COLLECTION PROTOCOL*

- The data collectors will be trained on conducting the interviews and recording data. The training will include role-playing and simulations. Training will cover how to respond to adverse events.
- The data safety and monitoring plan will be shared with the clinicians. For example, they will be trained on how to differentiate an active suicide crisis from a person who has suicide intent.
- Data collectors will receive ongoing supervision.
- The study team will make appointments for assessments when there will not be distractions for the participants.
- Data will be complete because our research assessors are asking participants the questions. Participants are not completing paper and pencil questionnaires, wherein they could accidentally skip responses.

### 13. DATA SECURITY FOR AVIVA

#### 13.1 *CYBERSECURITY AND DATA COLLECTION*

Data will be collected on a platform built on the fundamental principle of anonymity with security and privacy engineered into the core design. This includes (1) applying a security framework, and (2) ensuring data segregation of Patient Health Information (PHI). The data will not retain participant names when entered into our system and will only be accessible by authorized users. Study measures to ensure cybersecurity and data protection include:

- Unique password-protected user accounts.
- Detailed user account enrollment. When users begin the enrollment process and have provided their access code, they will be prompted to fill in their identity information, including their name, date of birth, email address, etc., and a personal password to protect their account. The combination of both their enrolled phone number and personal password will allow them to access the application on a supported mobile device.

- Strong password requirements. User passwords will be required to have: 1) 8 or more characters in length; 2) a mixture of both uppercase and lowercase letters; 3) a mixture of letters and numbers; and 4) at least one special character (e.g., ! @ # ?).
- Security and penetration testing.

